### Study design

As shown in Fig. 1, this study is a three-arm open randomized controlled trial consisting of three groups. The interventions are fire needle *plus* cupping (FC) in group A, famciclovir *plus* gabapentin (FG) in group B, and fire needle *plus* cupping *plus* famciclovir (FCF) in group C. After a randomization selection process, group A and group C received a total of 7 treatment sessions of fire needle cupping therapy within 1 week trial time. The administration of gabapentin depends on the needs of the patient of group B. In addition, if the acute pain cannot be endured, patients will be given temporary analgesic medicine.

**Fig. 1 Fig1:**
[figure not shown]
The flow chart of the trial

The visual analogue scale (VAS) scores, symptoms, and physical scores are obtained for pre- and post-treatment periods. The concentrations of SP and β-Ep in peripheral plasma will also be detected, and demand for temporary analgesics and side effects of the patients are recorded daily. As the final stage, after 6 months, the participants are to be followed up for postherpetic neuralgia, 6 months after treatment (Fig. 2).

**Fig. 2 Fig2:**
[figure not shown]
The time schedule of this trial

### Participants and recruitment

This study aims to recruit 105 patients by posting public posters in both local dermatology and acupuncture clinics and the website of the Sixth Affiliated Hospital of Kunming Medical University. When potential participants have read the poster, they can contact the dermatologists [name] and [name] through the contact phone number indicated on the poster. Potential patients then got enrolled and signed the consent form if they meet the inclusion criteria by the assessment of dermatologists. Meanwhile, a randomized grouping technique has been conducted. While preparing and unpacking all relevant information, [name] is responsible for such matter. The first formal trial recruitment began in November 2018. The assistant researcher will assess and record the baseline status of the participants (Table 3).

In order to achieve an adequate enrollment rate, we have developed two attractive offerings to gather patients’ attention as well as publicize recruitment notices (Fig. 3). They are as follows: First, all treatment and cost under this trial are free of charge for selected patients *r*. Second, if participants have postherpetic neuralgia 6 months later, they are entitled for another 10 sessions of free comprehensive acupuncture treatments *t*.

**Fig. 3 Fig3:**
[figure not shown]
The schedule of enrollment, interventions, and assessments (according to the SPIRIT statement 2013). VAS, visual analogy score; QS, quantitative score

### Randomization and allocation concealment

Block setting: 105 participants are numbered 1–105 according to the time of participation, the block length is 6, and 16 blocks are set.Obtaining random numbers: start with any two-digit number in the random number table, and take 105 numbers to the right.Grouping: 6 random numbers of each block are sorted from small to large, sorts 1 and 2 are group A, sorts 3 and 4 are group B, and sorts 5 and 6 are group C.Random group concealment: the grouping conditions of participants are packed into 105 envelopes, and all the envelopes are numbered in order and sealed. To ensure the randomization process, the serial number will be printed on the outside of the opaque envelope and the assignment of the group will be sealed on the inside of the envelope.

[name], an otolaryngologist at the Sixth Affiliated Hospital of Kunming Medical University, is responsible for the above matters, and she does not get involved in the process of treatment and the data collection of this study.

The envelope will be opened according to the patient’s serial number, and the dermatologists will be responsible to inform patients by phone on their random number and assignment.

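### The randomisation scheme has 96 block slots for 105 patients, and its constant block length could let recruiting dermatologists deduce some allocations

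*Protocol article*

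**What the plan says.** The protocol article, under *Randomization and allocation concealment*, sets out the procedure in full:

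- Patients: "105 participants are numbered 1–105 according to the time of participation".
- Blocks: "the block length is 6, and 16 blocks are set".
- Random numbers: "start with any two-digit number in the random number table, and take 105 numbers to the right".
- Assignment within a block, after ranking its six numbers: "sorts 1 and 2 are group A, sorts 3 and 4 are group B, and sorts 5 and 6 are group C".
- Envelopes: "the grouping conditions of participants are packed into 105 envelopes". They are opaque, sealed and serially numbered. A doctor who takes no part in treatment or data collection prepares them.
- Release of the assignment: "the dermatologists will be responsible to inform patients by phone on their random number and assignment".

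Under *Participants and recruitment*, patients enter the trial "if they meet the inclusion criteria by the assessment of dermatologists". *Study design* describes the trial as open. The abstract promises three groups in equal proportion.

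**The concern.** Two things look wrong.

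First, the block count does not fit the three other counts in the same section. The only rule that turns random numbers into arms works on a block of six, and nine of the envelopes belong to no such block. A reader cannot tell from the text how those nine assignments were or will be made.

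Second, every block described holds exactly two patients per arm, with no variation in length. The role that decides who enters is also the role that learns each patient's arm. In an open trial, someone who knows the earlier arms in a block can narrow down the later ones without touching an envelope. If that influenced who was enrolled, or when, the arms could differ at baseline. Randomisation carries much of the weight here: the *Discussion* concedes that there is no sham arm and that patients and acupuncturists cannot be blinded. The primary outcome is a patient-rated pain score.

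**Working it through.** **Where 96 and 105 come from.** *Sample size estimation* uses n = 2λ / (2·arcsin√p_max − 2·arcsin√p_min)², with p_max = 0.80, p_min = 0.378, alpha 0.05 and power 0.90. The article does not print λ. I take the noncentral chi-square value for three groups (2 degrees of freedom), λ = 12.654.

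- Arcsine difference = 0.890.
- n = 2 × 12.654 / 0.890² = 31.95, so 32 per group and 3 × 32 = 96. This matches the article.
- 96 × 1.09 = 104.6, so 105, which also matches.

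The number to be randomised is therefore 105, and 96 is the total before the dropout allowance.

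**Coverage of the list.**

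- Slots provided: 16 × 6 = 96.
- Slots needed: 105.
- Without a block: 105 − 96 = 9, and 9/105 = 8.6%.
- 105/6 = 17.5. Seventeen blocks give 102 and eighteen give 108, so no whole number of blocks of 6 gives 105.
- If an 18th block were cut after three patients, each arm would have 34 (from 17 full blocks) plus 0, 1 or 2, so 34 to 36.

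**Predictability.** Assume an observer who knows that each block is 2:2:2 and knows every earlier assignment in it. There are 6!/(2!·2!·2!) = 90 equally likely orders. By slot:

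| Slot | Next arm certain | At least one arm ruled out | Best guess correct |
|---|---|---|---|
| 1 | 0 | 0 | 1/3 = 0.333 |
| 2 | 0 | 0 | 2/5 = 0.400 |
| 3 | 0 | 0.2 | 2/4 = 0.500 |
| 4 | 0 | 0.6 | 0.4 × 1/3 + 0.6 × 2/3 = 0.533 |
| 5 | 0.2 | 1 | 0.2 × 1 + 0.8 × 1/2 = 0.600 |
| 6 | 1 | 1 | 1.000 |
| Mean | 1.2/6 = 20% | 2.8/6 = 47% | 3.367/6 = 56% |

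The chance that all three arms are still open at slot 4 is 2 × 2 × 2 / C(6,3) = 8/20 = 0.4. The chance that the last two slots belong to the same arm is 3/C(6,2) = 3/15 = 0.2. Over the 16 stated blocks, 16 × 1.2 = 19.2, or about 19 of 96 allocations, would be certain. Pure chance gives a best-guess rate of 33%.

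**The case against.** **On the count.** The section draws 105 numbers and fills 105 envelopes, so slots 97 to 105 do have random numbers and sealed assignments. A misprinted block count, or an undescribed top-up for dropout, would explain the gap, and the match with the pre-dropout total of 96 makes either plausible. This stands. A reader might infer that nine patients were allocated wrongly or with bias, and the article does not show that. It shows only that the written rule does not reach them. Nor is the possible departure from 35 per arm important, since it is about one patient.

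**On predictability.** The envelopes are sealed and opaque, the preparer is independent, and *Blinding* states an intention to conceal the grouping. More than one dermatologist recruits, and nothing says that each sees the other's assignments. Nothing says that they know the block length; its appearance in an article does not show that recruiters knew it during enrolment. The pain criterion is scored by the patient, so it is not obvious how a dermatologist would move it. Most of this stands as a limit on certainty. It does not remove the concern. Envelopes hide the next assignment but do not prevent deduction from earlier ones. The concealment described under *Blinding* cannot extend to dermatologists who must pass on the assignment. Some entry criteria also call for clinical judgement.

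**On ties.** A reader might also infer a flaw from the use of two-digit random numbers, which can tie within a block with no tie rule given. The article does not support treating this as a defect. It is operational detail that a full protocol may hold, and an independent person prepares the list, so resolving a tie gives recruiters no influence.

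**Conclusion.** The count is a definite error in the article: 96 block slots for 105 patients, with 9 (8.6%) outside the stated allocation rule. This needs no assumption and should be corrected.

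The predictability concern is conditional. The figures of 20%, 47% and 56% are upper bounds that assume recruiters know or infer the constant block length and follow every earlier assignment in order. The article neither states nor excludes this. A reader might infer that the dermatologists do see all allocations and can foresee the next one, or that selection bias has occurred; the documents support only the possibility. It merits a cheap precaution, with less urgency than the count. The sample size itself is not in question here.

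**What to change.** 1. Correct the scheme so that it covers all 105 numbers, and state the rule for 97 to 105.
2. For envelopes not yet used, have the independent list-holder generate the remaining list with block sizes in multiples of 3, in random order and withheld from recruiting staff. For a full list, 10 blocks of 6 and 5 blocks of 9 give 60 + 45 = 105, with 20 + 15 = 35 per arm. If the list changes after k complete blocks of 6, the remaining 105 − 6k numbers are still a multiple of 3.
3. If blocks of 6 are kept, prepare 18 blocks (108 envelopes). This repairs coverage but not predictability.
4. Release each assignment only after eligibility and consent are recorded, preferably by the list-holder and not by the dermatologist who decided eligibility.
5. *Participants and recruitment* puts the start of recruitment in November 2018, while *Trial status* gives 10 October 2019. Some envelopes may therefore already be used. If so, leave those assignments as they are and report how numbers 97 to 105 were allocated.

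The cost is a little extra work on the list, a change in who communicates the assignment, and possibly an imbalance of about one patient per arm.

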### Blinding

In order to eliminate operational shortcoming of blinding issues since treatment for FC and FCF group could not be performed blind, we will, instead, first conceal information related to randomized grouping and the results associated with the grouping of subjects, and then, we seek to provide sensory tests (outcome evaluators), data inspectors, and statistical analysts who are not aware of the detailed grouping and treatment of subjects as blind.

### Participating physicians

Participating physicians in the trial are doctors selected from the departments of dermatology and acupuncture and moxibustion at the Sixth Affiliated Hospital of Kunming Medical University. As acupuncturists are responsible for the treatment of FC and FCF, they are all highly qualified and have received a master’s degree in acupuncture and moxibustion as well as have undergone training in unified standardized operation plan.

### Patient and public involvement

Patients and/or public were not involved in the design of this study.

### Participants

#### Inclusion criteria

Eighteen to 60 years old, with no gender difference.Skin rash and clustered blister in asymmetrical skin area.Precursor symptoms such as general discomfort and fatigue before rash.Nervous pain in the affected area, skin hypersensitivity.The rash is distributed along the innervated area.Unilateral, not exceeding the midline of the body.Pain intensity as assessed by VAS (0–100 mm) of 50 mm δ pain intensity δ80 mm.

#### Exclusion criteria

Insulin-dependent diabetes mellitus or other diseases that affect peripheral sensitivity (e.g., polyneuropathy, chronic pain syndrome)Bleeding tendency (e.g., taking anticoagulants, coagulation dysfunction, thrombocytopenia)Pregnancy or lactationSurgery within the past 3 monthsDiseases affecting quality of life (e.g., cancer, paralysis)Mental illness (e.g., depression, schizophrenia, dementia) or severe heart/lung/kidney diseaseExposure to fire needle, cupping, painkillers, or other complementary and alternative treatments for this disease prior to treatmentContraindications for famciclovir, gabapentin, mecobalamin, paracetamol, tramadol, dextrozine, fire needles, and cupping

### Dropout

#### Case dropout

Subjects experienced other comorbidities, complications, or special physiological changes during the trial. They are classified as not suitable to continue the trial.During the trial, serious adverse events and important adverse events occur in the subjects, so they are not suitable to continue the trial, and investigators decide to withdraw.Subjects have poor compliance. Medication compliance is calculated using the tablet counting method. Medication compliance = dose taken/prescription dose × 100%; medication compliance < 80% or missed fire needle plus cupping treatment ≥ 1 time is defined as poor compliance.Violation of the test plan. Subjects change or add drugs other than the study protocol, and received other treatments other than the study protocol during the trial period.The subject withdrew out by himself.Lost to follow-up at the final stage.

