### Intervention

#### Group A

This group will be treated with only FC.
Acupoints: the main points are Ashi points (lesion area), corresponding nerve segment Jiaji points, and branch ditch points (SJ6); matching points are selected according to syndrome differentiation, pattern of dampness-heat in the liver meridian with Yang Ling Quan (GB34), pattern of dampness-heat in the spleen meridian with Yin Ling Quan (SP9), and pattern of obstruction of collaterals by blood stasis with blood sea (SP10).Appliances: medium-sized fire needle (diameter 0.4 mm), large-sized fire needle (diameter 0.65 mm), glass fire cup no. 1–5, medical cotton ball, alcohol lamp, lighter, iodophor, etc.Operational methods: routine disinfection of the skin with iodophor with the order of the head, middle, and tail of herpes will be carried out firstly. Holding 95% alcohol lamp by the left hand close to the needle, and to burn the needle in the right hand to whitening by the external flame of the fire, acupuncturist will prick the head of the herpes cluster. Then, the needles will be pricked into the blisters or rashes quickly from the surface of the skin to the base of the herpes. Pricking early-onset herpes at first, for larger pustules or blood blisters (diameter ε0.5 cm) with a large-scale fire, acupuncturist will extrude blister fluid with disinfection cotton ball after puncture, and then cup with a suitable size of glass fire cup for 5–10 min. If the area of the herpes cluster is too large, more than one cup can be used. The remaining acupuncture points are treated with fire needle pricking, and each acupuncture point should be pricked three times. Finally, the skin should be sterilized with iodophor more than one time. The treatment should be performed once a day for a total of 7 days.Skin care: after treatment, the iodophor is used to clean and disinfect the skin and to keep the patient’s skin dry and clean during the treatment.Course of treatment: the course of treatment is 1 week and from one to seven times. If there is no pain any more after one time of FC treatment, the course is just one time. Meanwhile, if the patient is still suffering pain, the FC will continue once a day unless the pain disappears. All the treatments will not be more than seven times no matter the pain or not.

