#### Statistical analysis

The purpose of this study is to confirm whether the therapeutic effect of experimental therapy (fire needle cupping) is different from that of reference therapy (famciclovir plus gabapentin and fire needle cupping plus famciclovir). SPSS 20.0 statistical software will be used for data analysis. When the main efficacy indicators of individual subjects are missing, the last observation carried forward will be conducted, and the non-main efficacy indicators will not be carried forward. The mean ± standard deviation is used for statistical description of measurement data, and the frequency (constituent ratio) is used for statistical description of counting data. The baseline characteristics will be recorded as in Table 3. The group *t* test (Bonferroni method) will be used to compare the measurement data between groups. All reported *P* values will be two-tailed with 95% confidence intervals. The value of *P* ≤ 0.05 will be considered statistically significant. PPS analysis and Fas analysis will be performed at the same time. SS analysis is used for safety evaluation.

**Table 3 Tab3:** Baseline characteristics

Characteristics	Value
Age, mean ± SD, year	
Gender, *n* (%)	
Male	
Female	
Onset days, mean ± SD, days	
VAS score, mean ± SD	
Quantitative score, mean ± SD	

Onset days are the time from the patient’s onset of pain or rash to inclusion

Quantitative score is quantitative score of symptoms and signs

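### One missed fire needle plus cupping session makes a patient a dropout while up to a fifth of drug doses may be missed; what counts as missed is unclear, and loss at 6 months is also dropout

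*Protocol article*

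**What the plan says.** **Compliance.** The list under Case dropout in the protocol article includes "Subjects have poor compliance. Medication compliance is calculated using the tablet counting method". The measure is "Medication compliance = dose taken/prescription dose × 100"%, and the limit is "medication compliance < 80% or missed fire needle plus cupping treatment ≥ 1 time is defined as poor compliance". Group A receives FC only, group B famciclovir plus gabapentin, and group C FC plus famciclovir.

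**Number of sessions.** Study design says that "group A and group C received a total of 7 treatment sessions of fire needle cupping therapy within 1 week trial time", and the Abstract also gives seven. The Group A section gives a daily treatment for seven days under its operational methods. Its course-of-treatment item then allows any number from one to seven, ending when the pain has gone: "If there is no pain any more after one time of FC treatment, the course is just one time". The Discussion adds that the number of FC treatments is not strictly held.

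**Late loss.** The same dropout list includes "Lost to follow-up at the final stage". Study design explains that stage: "As the final stage, after 6 months, the participants are to be followed up for postherpetic neuralgia". The primary outcome is the change in visual analogue scale (VAS) pain from before to after the one-week treatment.

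**Analysis.** "PPS analysis and Fas analysis will be performed at the same time", with last observation carried forward for missing main efficacy data. The section on managing dropouts asks for a last laboratory test so that they can still be analysed.

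**The concern.** Three stated rules decide who is called a dropout, and each has a problem.

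- The adherence limit is unequal. FC tolerates no missed session, whereas drug treatment tolerates up to 20% of the prescribed dose. Because the arms differ in which treatment they receive, the chance of being classed as a dropout differs by arm by construction, in an open trial.
- A missed session has no single reference. If seven sessions is the reference, a patient in A or C whose pain goes early, and whose course therefore stops, has missed sessions and becomes a dropout. Classification would then depend on pain, which is the primary outcome.
- Loss at the 6-month follow-up comes long after the primary outcome is complete, yet it turns a patient with full week-1 data into a dropout.

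At stake is any analysis that leaves these patients out. Such exclusions happen after randomisation, may differ by arm and may relate to response. They would also draw on a dropout allowance of only three patients per arm.

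A lesser point is that gabapentin in group B is raised according to the patient's needs, so the prescribed dose in the compliance ratio varies between patients.

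**Working it through.** **1. The plan's own figures.** Sample size estimation gives alpha 0.05, beta 0.1, P_max = 0.80, P_min = 0.378 and the arcsine formula. It does not print lambda; I took the noncentral chi-square value with 2 degrees of freedom for 90% power, 12.654.

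- Arcsine difference: 2·asin(√0.80) − 2·asin(√0.378) = 0.8900
- n = 2 × 12.654 / 0.8900² = 31.95, so 32 per group and 96 in all. This reproduces the plan.
- Allowance: 105 − 96 = 9 patients, which is 9/105 = 8.6% of those randomised, or 3 of 35 per arm.

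**2. The two limits on one scale.**

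- FC, seven sessions: one missed leaves 6/7 = 85.7%, classed as poor compliance.
- Famciclovir, 3 × 7 = 21 doses: four missed leaves 17/21 = 81.0%, acceptable; five missed leaves 16/21 = 76.2%, poor.

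**3. Share classed as poor compliers.** The article gives no miss rate, so q, the chance of missing one session or dose, is an assumption, varied from 1% to 10%. Misses are taken as independent and all seven sessions as due.

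- A: 1 − (1 − q)^7
- B, famciclovir only: P(Binomial(21, q) ≥ 5)
- C: 1 − (1 − A)(1 − B), failing either limit
- B, if whole days of doses are missed: P(Binomial(7, q) ≥ 2), because one lost day leaves 18/21 = 85.7% and two leave 15/21 = 71.4%
- FC under a common 80% limit: also P(Binomial(7, q) ≥ 2), because 6/7 passes

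| q | A | B, single doses | B, whole days | C | FC under common 80% limit |
|---|---|---|---|---|---|
| 1% | 6.8% | <0.01% | 0.2% | 6.8% | 0.2% |
| 2% | 13.2% | <0.01% | 0.8% | 13.2% | 0.8% |
| 5% | 30.2% | 0.3% | 4.4% | 30.4% | 4.4% |
| 10% | 52.2% | 5.2% | 15.0% | 54.7% | 15.0% |

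Gabapentin is not in the B columns, because its prescribed dose is not fixed.

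**4. Against the allowance.** The FC rule alone uses up 3 of 35 when 1 − (1 − q)^7 = 3/35, that is q = 1 − (32/35)^(1/7) = 1.27%. At q = 5%, 35 × (1 − 0.302) = 24.4 compliant patients are expected in A.

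**5. Sensitivity to the number of sessions due.** If only four sessions fall due, q = 5% gives 1 − 0.95^4 = 18.5% instead of 30.2%.

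**6. The session statements side by side.** The Abstract, Study design and the operational methods for Group A give seven. The course-of-treatment item for Group A gives one to seven, depending on pain. The Discussion loosens the number again. Case dropout does not say against which of these a session is missed.

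**The case against.** A reader might go further than the article allows in four ways.

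- **That the PPS is biased by arm.** The article names the PPS and FAS but does not define either, and nowhere says that the PPS leaves out the listed dropouts. The definition may stand in a fuller document that is not shown. The FAS is run alongside, missing main efficacy data are carried forward, and a last test is sought on dropouts. This stands: bias by arm is conditional. It is still a fair risk, because a per-protocol set ordinarily excludes poor compliers and these are the only such criteria stated.
- **That the best responders become dropouts.** A missed session is usually one that was due, and if the course ends when pain has gone, nothing more is due. The article supports this reading as well as the one with seven as the reference. The outcome-dependent exclusion is therefore one of two readings.
- **That the 6-month item adds to a difference between arms.** It applies to all arms alike, so it creates no rule-based difference. Nor does the article say that such patients lose their week-1 VAS data.
- **That the allowance cannot cover these rules.** At a 1% miss rate the FC loss is 6.8%, inside the 8.6% allowance. The claim holds only above about 1.3%.

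Two further objections have some weight. A stricter limit for clinic-delivered sessions than for self-taken doses is partly a matter of choice. The benchmark of 32 comes from cure rates, not the VAS outcome, so setting 24 compliant patients against it says little about power for the VAS comparison. Neither removes the inconsistency in what counts as missed or the unequal limits.

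**Conclusion.** The concern holds in limited form. As written, the compliance rule treats FC and drug treatment unequally (no missed session of seven, against up to 4 of 21 famciclovir doses). It falls on A through FC, on B through drugs and on C through both. The reference for a missed session is contradictory. If it is seven, early responders in A and C become dropouts.

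If the PPS excludes these dropouts, exclusions would differ by arm and could depend on outcome. The direction cannot be told: losing early responders would count against FC, while losing poor responders who skip sessions would favour it.

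The size rests wholly on an assumed miss rate, independence and seven sessions due. Over rates of 1% to 5%, poor compliance is 6.8% to 30.2% in A and at most 4.4% for famciclovir in B, even with whole days missed. The allowance is exhausted at about 1.3% per session.

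The 6-month item is a separate fault, common to all arms: it labels as dropouts patients whose primary outcome is complete.

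**What to change.** 1. The investigators should reconcile the Abstract, Study design, Case dropout, Group A and Discussion on the number of FC sessions. Which schedule applies is theirs to settle.
2. Define a missed session as one that was due under the reconciled schedule but not attended.
3. For the PPS, use the same adherence threshold for sessions and doses, for example 80% of what was due, and state the denominator for gabapentin when its dose is raised by need. With seven sessions due and a 5% miss rate, the common threshold cuts poor compliance in A from 30.2% to 4.4%.
4. Keep poor compliers in assessment and in the FAS.
5. Treat loss at 6 months as missing data for postherpetic neuralgia only, with no effect on the week-1 analysis.
6. Name the FAS as the basis for the conclusion and the PPS as supportive.

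The cost is a change of wording in the dropout and analysis-set definitions, best made before analysis. The downside is a slightly less strict PPS. The sample size of 32 per group, 96 and 105 is unaffected.
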